## Abstract

**Background:**

Acquired brain injuries (ABIs) commonly cause cognitive-communication disorders, which can have a pervasive psychosocial impact on a person’s life. More than 135 million people worldwide currently live with ABI, and this large and growing burden is increasingly surpassing global rehabilitation service capacity. A web-based service delivery model may offer a scalable solution. The Social Brain Toolkit is an evidence-based suite of 3 web-based communication training interventions for people with ABI and their communication partners. Successful real-world delivery of web-based interventions such as the Social Brain Toolkit requires investigation of intervention implementation in addition to efficacy and effectiveness.

**Objective:**

The aim of this study is to investigate the implementation and effectiveness of the Social Brain Toolkit as a web-based service delivery model.

**Methods:**

This is a mixed methods, prospective, hybrid type 2 implementation-effectiveness study, theoretically underpinned by the Nonadoption, Abandonment, Scale-up, Spread, and Sustainability (NASSS) framework of digital health implementation. We will document implementation strategies preemptively deployed to support the launch of the Social Brain Toolkit interventions, as well as implementation strategies identified by end users through formative evaluation of the Social Brain Toolkit. We will prospectively observe implementation outcomes, selected on the basis of the NASSS framework, through quantitative web analytics of intervention use, qualitative and quantitative pre- and postintervention survey data from all users within a specified sample frame, and qualitative interviews with a subset of users of each intervention. Qualitative implementation data will be deductively analyzed against the NASSS framework. Quantitative implementation data will be analyzed descriptively. We will obtain effectiveness outcomes through web-based knowledge tests, custom user questionnaires, and formal clinical tools. Quantitative effectiveness outcomes will be analyzed through descriptive statistics and the Reliable Change Index, with repeated analysis of variance (pretraining, posttraining, and follow-up), to determine whether there is any significant improvement within this participant sample.

**Results:**

Data collection commenced on July 2, 2021, and is expected to conclude on June 1, 2022, after a 6-month sample frame of analytics for each Social Brain Toolkit intervention. Data analysis will occur concurrently with data collection until mid-2022, with results expected for publication late 2022 and early 2023.

**Conclusions:**

End-user evaluation of the Social Brain Toolkit’s implementation can guide intervention development and implementation to reach and meet community needs in a feasible, scalable, sustainable, and acceptable manner. End user feedback will be directly incorporated and addressed wherever possible in the next version of the Social Brain Toolkit. Learnings from these findings will benefit the implementation of this and future web-based psychosocial interventions for people with ABI and other populations.

**Trial Registration:**

Australia and New Zealand Clinical Trials Registry ACTRN12621001170819; https://anzctr.org.au/Trial/Registration/TrialReview.aspx?ACTRN=12621001170819, Australia and New Zealand Clinical Trials Registry ACTRN12621001177842; https://anzctr.org.au/Trial/Registration/TrialReview.aspx?ACTRN=12621001177842, Australia and New Zealand Clinical Trials Registry ACTRN12621001180808; https://anzctr.org.au/Trial/Registration/TrialReview.aspx?ACTRN=12621001180808

**International Registered Report Identifier (IRRID):**

DERR1-10.2196/31995

## Introduction

### Background

More than 135 million people worldwide currently live with acquired brain injuries (ABIs), including traumatic brain injury and stroke [1]. ABIs commonly cause cognitive-communication disorders in which underlying problems with working memory, organization, executive function, self-regulation, or a combination of these, affect the communication skills needed for everyday exchanges such as conversations, explanations, and stories [2]. Cognitive-communication disorders can thus have a pervasive impact on a person’s social participation and relationships [3], employment [4,5], and mental health [6], while presenting concurrent health, psychosocial, and economic challenges for their families and communities [7-9].

The growing psychosocial burden of ABI increasingly surpasses the global rehabilitation service capacity to address it [1], including national-scale shortages in public speech-language pathology services to manage communication difficulty [10]. Inversely, families of people with ABI, particularly from rural and remote areas, experience logistical and access challenges when seeking face-to-face health care, leading carers to express their need for locally accessible support [11]. The equitable and scalable delivery of communication rehabilitation for people with ABI is therefore a global health service challenge [1], demanding consideration of alternative and complementary service delivery models to meet the psychosocial needs of this population and their communities now and into the future.

In response to these challenges, an evidence-based suite of web-based interventions known as the Social Brain Toolkit [12] is currently in development. The project was cocreated with stakeholders, including people with ABI and their communication partners, clinicians, partnering organizations, and policy makers. These stakeholders have been attending, and are included in, regular steering and advisory committee meetings. They have provided feedback on early prototypes and have been involved in the planning of implementation strategies and now the formative evaluation of the Social Brain Toolkit products. The aim of the Social Brain Toolkit is to provide scalable communication training to people with ABI and their communication partners, including family members, friends, partners, paid support workers, and clinicians. The Social Brain Toolkit comprises 3 web-based interventions: (1) convers-ABI-lity, a conversation skills training program for adults with ABI and familiar communication partners such as family members, partners, and friends; (2) interact-ABI-lity, web-based communication training for unfamiliar communication partners of people with ABI, such as paid support workers and the general public; and (3) social-ABI-lity, social media training for people with ABI seeking to communicate and connect on the web. interact-ABI-lity and social-ABI-lity are self-directed web-based courses, whereas convers-ABI-lity includes self-directed web-based content between telehealth sessions with a speech-language pathologist. The need for and format of these communication training courses were identified together with stakeholders, including people with ABI and their communication partners, with the aim of improving the quality of life and psychosocial outcomes of people with ABI and their communities.

The communication skills of communication partners can have a positive or detrimental effect on the communication skills of people with ABI [13-15]. Therefore, interact-ABI-lity and convers-ABI-lity deliver an evidence-based [16] intervention known as communication partner training (CPT), which involves training communication partners to facilitate the communication [17] of the person with ABI. CPT is recommended in international guidelines as best practice management of cognitive-communication disorders after ABI [18,19], and the convers-ABI-lity intervention delivers the core therapeutic content of the existing efficacious CPT programs TBI Express [20] and TBIconneCT [21,22]. convers-ABI-lity is a conversion and streamlining of the content of these programs into both asynchronous self-directed activities and synchronous telehealth speech-language pathology sessions. interact-ABI-lity delivers CPT as an asynchronous, self-directed web-based educational intervention.

In addition, the Social Brain Toolkit contains the social-ABI-lity intervention, which provides people with ABI with training in communication through social media. This is because people with ABI who use social media for connection are likely to experience difficulties in web-based interactions that are similar to those experienced in real-world interactions [23]. The social-ABI-lity intervention in the Social Brain Toolkit is an educational intervention based on new recommendations to support and train people with ABI in the safe and effective use of social media, with a view to increasing their social participation, enabling recovery of social communication skills, and promoting a sense of self or identity after ABI [24].

Web-based access to psychosocial interventions such as the Social Brain Toolkit are promising not just for the possibility of improving the scalability and accessibility of interventions, but also for their potential to reduce inequities in access to psychosocial support. Even before global shifts to web-based health care during the COVID-19 pandemic [25], people with ABI frequently accessed language and cognitive training on the web, with older patients and rural residents even more digitally engaged than younger and urban users [26]. When delivered on a national scale, equivalent web-based service delivery models in mental health have demonstrated the ability to overcome entrenched health care access barriers such as socioeconomic and indigenous status, and to enable access to users who otherwise do not access traditional face-to-face care [27,28]. However, web-based service delivery models face numerous implementation challenges. Even clinically effective digital health interventions struggle to be sustained as a long-term service delivery option [29] for reasons beyond their clinical effectiveness, including costs and workflow changes associated with their delivery [30]. Although there is an established and varied evidence base exploring web-based psychosocial interventions [31,32], there is limited implementation science research over and above these clinical trials to determine how these interventions might be successfully implemented and sustained as part of routine clinical care [31]. Therefore, a specific focus on implementation, especially in early research collaboration with end users, has been recommended for future research into web-based psychosocial care [27-31].

Therefore, real-world evaluation of the implementation of the Social Brain Toolkit interventions demands (1) collaborative involvement of end users, (2) a hybrid implementation-effectiveness research design [33] to expedite the incorporation of implementation learnings into intervention design, and (3) a theoretical underpinning in a digital health implementation framework that reflects the complexity of real-world implementation. Thus, this hybrid implementation-effectiveness study will be underpinned by an implementation theory that is both specific to digital health and based on a complexity approach: the Nonadoption, Abandonment, Scale-up, Spread, and Sustainability (NASSS) framework of eHealth implementation [34-36]. This framework will be used to support the more comprehensive identification of real-world complexities in the scale-up, spread, and sustainability of the Social Brain Toolkit.

### Aims

In this study, formative evaluation of the implementation of the Social Brain Toolkit by end users in the community will be used to guide intervention development and implementation [37] to support these interventions to reach and meet community needs in a feasible, scalable, sustainable, and acceptable manner. Therefore, guided by domains of the NASSS framework [34,35], in this hybrid implementation-effectiveness study, we aim to answer the following implementation questions:

Who uses these interventions and what are their characteristics (domains 1 and 4)? What implementation strategies can be used to improve intervention reach?In what geographical locations and health care and social contexts are the interventions used (domains 3 and 5-6)? What implementation strategies can be used to improve intervention reach?Do users complete the interventions as intended (domain 4)? Why or why not? What implementation strategies can be used to improve intervention adherence and fidelity?How usable is the technology for those completing the interventions (domain 2)? What changes can be made to improve usability?What barriers, facilitators, and workarounds do users experience when completing these interventions (domains 1-7)? What strategies, facilitators, and workarounds can be used to improve future implementation?How satisfied are users with the interventions (domain 3)? What changes can be made to increase user satisfaction?What is the cost of delivering each web-based intervention, and how does this compare with face-to-face delivery (domain 3)?

We seek to determine intervention effectiveness as follows:

Do people who complete the interact-ABI-lity course have improvements in their self-efficacy and knowledge about communicating with people with ABI?Do people who complete the social-ABI-lity course have improvements in their self-efficacy and knowledge about communicating safely and successfully on social media?Do people who complete the convers-ABI-lity program have improved communication and quality-of-life outcomes?

## Methods

### Design

This study uses a prospective hybrid type 2 implementation-effectiveness design [33] and is registered on the Australia and New Zealand Clinical Trials Registry: interact-ABI-lity ACTRN12621001170819 (Universal Trial Number [UTN] U1111-1266-6628); social-ABI-lity ACTRN12621001177842 (UTN U1111-1268-4909); and convers-ABI-lity ACTRN12621001180808 (UTN U1111-1268-4849). The Social Brain Toolkit is well suited to a hybrid implementation-effectiveness design [37] because its interventions present minimal risk [16], with indirect evidence supporting effectiveness [22-24] and strong face validity supporting applicability to a web-based delivery method [21,22]. A prospective hybrid type 2 design especially reflects a collaborative ethos because it allows formative evaluation by end users to inform the refinement and improvement of both the clinical interventions and their implementation processes [37]. Preemptive implementation strategies will be devised during intervention development, including through consultation with people with ABI, communication partners, and clinicians supporting people with ABI, and people with experience implementing digital health [38], as well as reference to current implementation science literature [39]. Additional user-identified implementation strategies will be determined as part of the formative evaluation processes in this study, rather than solely a priori, in keeping with our collaborative ethos and approach. The deployment of additional user-identified strategies will enable us to identify and potentially address persisting and unanticipated implementation barriers or shortcomings of our preemptive implementation strategies.

### Data Collection

To obtain these data, we will use a mixed methods design for both implementation (Multimedia Appendix 1) and effectiveness (Multimedia Appendix 2) [40-42] data collection.

#### Interviews

Intervention usability and user experience and satisfaction will be formatively evaluated through interviews. The first 30 minutes of the 90-minute interview will involve a think-aloud [43] review of the user interface through screen sharing of the web-based platform. The think-aloud method is a robust and flexible research technique to test usability by providing valuable and reliable information of users’ cognitive processes while completing a task [43]. This think-aloud task will be followed by a 60-minute qualitative interview, with interview questions developed using the NASSS framework of digital health implementation [34] to prompt discussion of multiple issues within this time frame (see Multimedia Appendices 3-7 for interview protocols). We will conduct the interviews as soon as possible after a user’s completion of the course to facilitate recollection of the intervention experience. We will conduct the interviews individually and with communication partners, depending on participant preference and availability. Data collection will occur entirely on the web, with interviews conducted through secure videoconferencing on Microsoft Teams (Microsoft Corporation) software [44]. The interview will be audio and video recorded using the built-in recording functions of the videoconferencing platform. Interview recordings will be transcribed verbatim for analysis.

#### Surveys

For all 3 interventions in the Social Brain Toolkit, we will use pre- and postintervention surveys within the intervention platforms to obtain implementation outcomes, including user demographic information, and qualitative and quantitative patient-reported experience measures (Multimedia Appendix 1). We will conduct the surveys completely on the web. The surveys are based on the NASSS framework domains (see Multimedia Appendices 8-10 for survey protocols). We will measure intervention effectiveness using questionnaires that probe patient-reported outcome measures such as self-ratings of confidence in communicating with someone with ABI or using social media (Multimedia Appendix 2).

#### Analytics

We will collect web analytics (Multimedia Appendix 1) for each intervention over a 6-month sampling frame. This will enable user fidelity and adherence to the interventions to be examined.

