#### Quantitative

We will prospectively measure implementation outcomes in relation to the following:

Preemptive strategies deployed to support the implementation of the Social Brain Toolkit at launch, devised through current implementation evidence [39] and stakeholder input from a separate study [38].Additional user-identified strategies subsequently obtained through formative evaluation of the interventions by end users.

To observe any potential influence of these implementation strategies and factors on implementation success and the time lag of impact, we will record the following:

A detailed description of each implementation strategy and its rationale.A detailed timeline of each strategy’s deployment.Effectiveness and implementation outcomes over time.

We will calculate descriptive statistics of implementation measures, including user demographic characteristics, satisfaction ratings, percentage completion, and total number of users (Multimedia Appendix 1). We will tabulate descriptive statistics stratified by time and by whether users complete the interventions. Descriptive statistical analysis will be conducted using RStudio software (RStudio Inc) [48].

Clinical assessment data for conversation skills and quality of life (Multimedia Appendix 2) [40-42] will be analyzed using the Reliable Change Index [49] to determine whether individual participants had any clinically significant changes. Patient-reported outcome measures for interact-ABI-lity and social-ABI-lity, such as self-ratings of confidence, will be analyzed using repeated measures analysis of variance, with 3 levels (pretraining, posttraining, and follow-up) to determine whether there is any significant improvement within this participant sample. These data will also be managed using appropriate statistical software such as Microsoft Excel 2016 (Microsoft Corporation) [47].

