### Participants

#### Inclusion and Exclusion Criteria for Users of interact-ABI-lity and social-ABI-lity

As social-ABI-lity and interact-ABI-lity are publicly available web-based courses, all users of the courses within the sample frame will be included in data collection and analysis of survey and analytic data, with no restrictions of inclusion and exclusion criteria. A minimum of 5 users of the social-ABI-lity course (ie, people with ABI) and interact-ABI-lity courses (ie, communication partners such as paid support workers, friends, and family members) will be invited to participate in further implementation interviews. This number of users interviewed is consistent with the think-aloud methods described in the study design [43], which are used to refine the usability of the courses. The internationally recognized industry standard [53] is for a minimum of 5 users to undergo a formative usability interview evaluation [53], because only so many users are required to identify up to 90% of the usability issues [54] before there are diminishing returns for the product cycle [53]. However, a maximum variation sample of these interviewees will be sought if and where possible.

If people with ABI completed the social-ABI-lity course with the assistance of a friend, partner, family member, or other individual, this person will also be invited through the course user to be interviewed together or individually, depending on individual preference or availability. Therefore, interview participants must meet the following criteria:

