### Participant Enrollment

At manuscript submission on July 13, 2021, 85 participants had enrolled in interact-ABI-lity, with 85 completed entry surveys, 6 course completions, and 8 completed exit surveys. No interview data had yet been collected. Data collection for interact-ABI-lity commenced on July 2, 2021, and is expected to conclude on January 2, 2022, after a 6-month sample frame of analytics. By July 13, 2021, 1 participant had been recruited to participate in the convers-ABI-lity study, with no data yet collected. Data collection is expected to commence on July 26, 2021, and conclude on March 26, 2022. By July 13, 2021, no participant had been recruited to participate in the social-ABI-lity study. Data collection is expected to commence on December 1, 2021, and conclude on June 1, 2022, after a 6-month sample frame of analytics.

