### Analysis and Findings

Data analysis will occur concurrently with data collection until mid-2022. Results are expected for publication during late 2022 and early 2023.

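### interact-ABI-lity and social-ABI-lity: including every user up to a fixed closing date biases crude completion down and leaves late enrollees without a follow-up score

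*Protocol article*

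**What the plan says.** The Analytics section sets the frame: "We will collect web analytics (Multimedia Appendix 1) for each intervention over a 6-month sampling frame". Participant Enrollment applies one closing date per course to data collection as a whole, not only to analytics. For interact-ABI-lity: "Data collection for interact-ABI-lity commenced on July 2, 2021, and is expected to conclude on January 2, 2022". For social-ABI-lity: "Data collection is expected to commence on December 1, 2021, and conclude on June 1, 2022, after a 6-month sample frame of analytics".

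The eligibility section for these two courses states that "all users of the courses within the sample frame will be included in data collection and analysis of survey and analytic data", and it applies no inclusion or exclusion criteria. The article gives no enrolment cut-off before the close and no minimum observation time.

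The Quantitative analysis section lists percentage completion among the descriptive implementation measures and adds: "We will tabulate descriptive statistics stratified by time and by whether users complete the interventions". The stated purpose of recording outcomes over time is to observe any influence of the implementation strategies and the time lag of their impact. The same section plans a repeated measures analysis of variance with three levels, the third being follow-up. The Clinical Outcomes section plans knowledge questions at follow-up as well. On timing, Analysis and Findings says: "Data analysis will occur concurrently with data collection until mid-2022".

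**The concern.** Enrolment is open for as long as the frame is open, and the frame closes for everybody on the same day. Observation time therefore shrinks steadily with enrolment date. A user who registers in the last week counts fully in the completion denominator but has at most a week to reach the numerator. A user who registers too near the close cannot supply the third measurement at all.

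Two results are at stake. The first is adherence, since whether users complete the interventions as intended is one of the article's implementation questions. A crude percentage at the close understates eventual completion, and a table by enrolment period would show a decline that comes only from the cut-off. Any strategy deployed during the frame acts on later users, so that decline could mask or reverse its apparent effect. The second is the three-level analysis, which would lose later enrollees. For social-ABI-lity, an analysis ending in mid-2022 leaves little time after June 1 to collect what is missing.

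**Working it through.** **Frame length.** July 2, 2021 to January 2, 2022 is 184 days. December 1, 2021 to June 1, 2022 is 182 days. Both match the stated 6 months (about 26 weeks).

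**Direction.** Let p be eventual completion and G(t) the chance that an eventual completer has finished within t of enrolling. A user enrolled at time s in a frame of length T is seen as complete with probability p × G(T − s). This is below p whenever G(T − s) < 1, which holds near the close for any positive completion time. The direction needs no outside figure.

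**Size.** The article gives neither time to complete, follow-up interval nor enrolment pattern. The inputs below are assumptions.

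*Completion, uniform enrolment.* Take exponential time to completion with mean m weeks. For a cohort with between a and b weeks left, observed completion is

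p × [1 − m(e^(−a/m) − e^(−b/m)) / (b − a)].

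With p = 30%, m = 4 and six cohorts of 26/6 = 4.33 weeks:
- Last cohort (a = 0, b = 4.33): 0.30 × [1 − 4(1 − 0.3385)/4.33] = 0.30 × 0.389 = 11.7%.
- All six, first to last: 30, 30, 29, 28, 24, 12%.
- Overall (a = 0, b = 26): 0.30 × [1 − 4(1 − e^(−6.5))/26] = 25.4%.

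If completion in the last cohort had truly risen to 40%, the table would show 0.40 × 0.389 = 15.6%, so a real gain would look like a fall.

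*Faster completion.* With m = 1 week, the last cohort reads 23% and the overall figure is 0.30 × (1 − 1/26) = 28.8%.

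*Enrolment pattern.* Take p = 50%, a median of 28 days to complete and T = 184 days.

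| Enrolment | Overall observed completion |
|---|---|
| Uniform | 39.1% |
| Front-loaded (density falling exponentially, mean 30 days) | 48.4% |

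Under front-loading, the last sixth of the frame holds only (e^(−153.3/30) − e^(−184/30)) / (1 − e^(−184/30)) = 0.4% of users. The overall figure is barely affected, although that small cohort is still truncated.

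*Follow-up.* With uniform enrolment, the share who cannot reach follow-up is (W + F)/26, where W is weeks to complete and F the follow-up interval in weeks:
- W = 2, F = 4: 6/26 = 23%.
- W = 6, F = 12: 18/26 = 69%.

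With instant completion and a 30-day interval it is 30/184 = 16%. With the front-loaded pattern, instant completion and a 91-day interval, it is 4%.

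**The case against.** Several points on the other side are sound, and they limit the claim.

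- **Late enrollees can finish.** Participant Enrollment reports 6 completions among 85 enrollees by July 13, 2021, day 11 of the frame. A reader might infer that late registrants cannot complete. The article shows that some users finish within 11 days, so the supported statement is that they may not have time.
- **Enrolment may be front-loaded.** At 85 users in 11 days, a constant rate would give 85/11 × 184, or about 1,420 users, yet Strengths and Limitations describes an initial limited release with a constrained sample size. A launch surge is plausible, and then the overall bias is small.
- **The meaning of time is open.** The artefactual decline appears if the tables are by enrolment period. If they are by calendar month of completion, late months include completions by earlier enrollees and the decline need not arise. It would go too far to say that the latest periods must look worst.
- **The timing of strategies is not given.** The article foresees deploying user-identified strategies, but its Conclusions also place changes from user feedback in the next version of the Toolkit. That such strategies act in the last months of the frame is not established.
- **Follow-up loss need not bias the result.** A reader might infer that the follow-up analysis is invalid or rests only on early adopters. The comparison is within person, so a calendar cut-off mainly costs precision. It biases the estimated change only if change differs by enrolment date.
- **The analysis is descriptive and the dates are expected ones.** No confirmatory trend test is planned, and the multimedia appendices may define the completion measure and follow-up interval.

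These points reduce the size and certainty of the harm but do not remove it. The include-everyone rule, the common closing dates and the percentage measure are stated in the article. A later analysis document can change how completion is calculated, but it cannot recover follow-up scores that were never collected.

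**Conclusion.** The point holds for interact-ABI-lity and social-ABI-lity. Followed as written, the plan gives a completion percentage that understates eventual completion, and it gives no follow-up score for users who enrol too close to the close. A false decline across time strata follows only if strata are enrolment periods.

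The size cannot be computed from the article. In the assumed scenarios, overall completion ranges from almost unaffected (48.4% against 50%) to clearly low (25% against 30%), with a last monthly cohort of 12% against 30%. The share unable to reach follow-up runs from 4% to 69%. These ranges rest on the assumed completion times, follow-up intervals and enrolment patterns.

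Because the Analytics sentence covers each intervention, a reader might extend the point to convers-ABI-lity. The documents do not support that. Its interviews concern a fixed pilot group of 10 people with ABI and their 10 partners, and its schedule differs: "Data collection is expected to commence on July 26, 2021, and conclude on March 26, 2022", which is 8 months. Its clinical outcomes are collected in a parallel study.

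**What to change.** **Completion.** Measure it from each user's enrolment date, in one of two ways: completion within a fixed number of weeks among users with at least that much observation, or a Kaplan-Meier time-to-completion curve censored at the frame end. Tabulate by enrolment cohort and say so in the Quantitative section. Cohort tabulation alone is not enough, because the fixed window or the censoring is what removes the artefact. This needs only enrolment and completion dates for each user, which should be available from the course records and analytics.

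**Three-level analysis.** Either keep the automated exit and follow-up surveys open after the frame closes for users enrolled inside it, for one course length plus one follow-up interval, or restrict the follow-up contrast to users enrolled early enough to reach it.

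**Cost.** Keeping the surveys open delays the social-ABI-lity data lock by some weeks and pushes against the mid-2022 end of analysis. Restricting the cohort causes no delay but gives a smaller follow-up sample.
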